A recent small study found that 24% of pediatric patients who were treated with a single dose of ondansetron for acute gastroenteritis in the ED reported experiencing recurrent emesis within 24 hours of discharge. We hypothesize that the use of a physician-dispensed, as needed home dosing regimen of ondansetron given to patients (in anticipation of recurrent emesis and risk of dehydration) may prevent a return to the ED. While a small 2010 study found no reduction in ED revisits after discharging patients’ home with a written prescription for ondansetron, the authors caution that they did not track the number of patients who actually filled their prescriptions. In 2002, Ramsook et al. conducted a single-centre, double-blinded, placebo-controlled trial involving 145 children, comparing six doses of ondansetron/placebo administered every 8 hours for two days (scheduled). Vomiting was reduced after the first dose was administered; however, no further benefit was seen following discharge (vomiting occurred in 42% administered ondansetron versus 46% administered placebo at 24 hours). In addition, at the 24 hour and 48 hour follow-ups, the median number of vomiting episodes remained zero, with no statistically significant difference between groups. During the 48 hours following ED discharge, children administered ondansetron had threefold more diarrhea than those in the placebo group (mean 7.7 versus 2.3 episodes). The revisit rate was also higher in the ondansetron group ( $P=0.05$ ). Of the four patients with revisits in the ondansetron arm, two returned with persistent vomiting and the other two with persistent diarrhea. Interestingly, providing a home dose of ondansetron to patients by the ED physician as part of discharge planning may/ promote compliance on an outpatient basis.

A second double-blinded, placebo-controlled trial of relevance was published by Yilmaz et al. in 2010, in which the authors provided participants ( $N=109$ ) with ondansetron/placebo every 8 hours for a total of 24 hours. In this study, although ondansetron administration reduced the frequency of vomiting following discharge (mean of 1.7 versus 0.2 episodes over 24 h;  $P<0.001$ ), its administration was also associated with an increase in the number of

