### 9.2 SAMPLE SIZE DETERMINATION

The primary analysis will be performed on a binary outcome: Development of moderate-to-severe disease. The power of this analysis is based on the proportion of patients with moderate-to-severe disease. Our pilot data indicate that 30% of patients will have moderate to severe disease following the index visit (personal communication with [name]). Furthermore, expert surveys indicated that an absolute risk reduction of 10% would constitute a minimal clinically-important difference (MCID). Therefore, our sample size calculation assumed a 30% event rate in the control group for which we desire to detect an absolute beneficial treatment effect of 10% with 90% power. Using a two-sided type I error of 0.05 and the hypothesized proportions yields a required total sample size of 784 patients. Our expected power, should we find different event rates in our 2 groups, is displayed in Table 2.0.

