## 9.4 STATISTICAL ANALYSES

### 9.4.1 GENERAL APPROACH

For the primary outcome, the significance level will be set at 0.05. The overall significance level for statistical tests on the secondary outcomes will be set at 0.05.

To control the overall significance level for the secondary outcomes, the significance level will be adjusted for multiple comparisons. Vomiting and diarrhea duration, vomiting and diarrhea frequency, proportion with vomiting, unscheduled healthcare provider visits, intravenous rehydration, and caregiver satisfaction will be subject to Holm's stepdown procedure. Specifically, the smallest of the eight p-values will be compared to a significance level of  $0.05/8$ . If significance is reached, the next-smallest p-value will be compared to  $0.05/7$ , and so on. The final p-value of the six will be compared to 0.05, assuming that all others are significant. Confirmatory and tertiary outcome results will not be adjusted for multiple comparisons, as these are more exploratory in nature.

A 95% confidence interval will be reported around estimates of the treatment effects of the primary and secondary outcomes.

All analytical models will be evaluated and adjustments will be made if any assumptions appear to be seriously violated.

Publication of the primary results will include reporting of key baseline characteristics overall, and by assigned treatment arm (active or placebo). These will include, but will not be limited to,

- Gender
- Age
- Season
- Weight

- Primary care physician access
- Daycare attendance
- Receipt of rotavirus vaccine
- Vomiting and diarrhea duration and frequency
- Presence of fever
- Prior ED visits, IV rehydration, hospitalization
- Baseline MVS
- Duration of symptoms prior to enrollment (<48 hours vs. 48 hours or more)
- Antibiotic usage during the 14 days prior to ED visit
- Hydration assessment (Clinical Dehydration Scale score)
- Need for hospitalization from initial ED visit

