#### 9.4.3 ANALYSIS OF THE SECONDARY ENDPOINT(S)

**Secondary outcomes** and how they will be assessed can be found below:

1. **Frequency of vomiting from study enrollment to day 7:** The total number of episodes of vomiting and diarrhea related to the presenting illness will be compared between groups (active and placebo). This data will be obtained from the study questionnaires performed on Day 0, 24, 48, and 168 (7 days) hours after enrollment. Questionnaires (telephone or email) will contain questions regarding vomiting presence, number of episodes, and vomiting cessation date and time. Frequency will be defined as the total number of episodes across the study duration and will not consider differences in the vomiting duration across participants.
2. **Duration of vomiting:** The total number of days the participant experiences vomiting from Day 0 to Day 7. This data will be obtained from the study questionnaires performed on Day 0, 24, 48, and 168 (7 days) hours after enrollment. Questionnaires (telephone or email) will contain questions regarding vomiting presence, number of episodes, and vomiting cessation date and time. A participant with a 24-hour break in symptoms will be assumed to have ceased vomiting.
3. **Proportion of participants who experience vomiting within 7 days of enrollment:** The proportion of participants will be determined using data from the participant questionnaires performed 24, 48, and 168 hours after enrollment (Time 0).
4. **Proportion of participants who require an unscheduled health care provider visit within 7 days of enrollment:** Return visits for unscheduled care to a health care provider related to vomiting, diarrhea, dehydration, fever, abdominal pain, or fluid refusal within 7 days, not including scheduled visits (e.g. reassessments, vaccinations, etc.) will also be measured using follow up questionnaires 24, 48, and 168 hours after enrollment. Return to care data will be confirmed by reviewing the participant's hospital chart. Not all data within a patient's medical record will be available to the research team therefore the questionnaires will be the primary source of this data.

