5. **Proportion of participants who require intravenous rehydration:** If the participant required an unscheduled health care visit (see #4 above), the participant will be asked additional questions related to intravenous (IV) insertion, treatment course, and disposition. Intravenous fluids administered at the index visit will not be included as part of this outcome.
6. **Caregiver satisfaction as measured by a 5-point Likert scale in the 48 hours following ED disposition:** Caregiver satisfaction with the therapy provided (oral ondansetron or placebo) in the 48 hours following ED disposition. This will be measured using a 5 point Likert scale on the questionnaire administered 168 hours after Time 0.

The analysis of secondary outcomes will be undertaken as detailed below:

1. **Frequency of vomiting from study enrollment to Day 7:** The total number of episodes of vomiting and diarrhea related to the presenting illness will be compared between groups (active and placebo) using a generalized linear model to compare differences between Poisson rates whilst adjusting for stratification.

2. **Duration of vomiting :** The total number of days the participant experiences vomiting from Day 0 to Day 7 will be compared using the Van Elteren test, stratified by center and duration of symptoms (pre-enrollment). If a number of patients still experience symptoms at the 7-day follow-up questionnaire, this will be tested using a suitable procedure to take account of censoring such as median regression or additive hazard models. Additional analyses involving this outcome will include linear regression models that adjust for possible effects of baseline characteristics.
3. **Proportion of participants who experience vomiting within 7 days of enrollment:** The proportion of participants with vomiting following enrollment will be compared using Mantel-Haenszel test stratified by site and weight.
4. **Proportion of participants who require an unscheduled health care provider visit within 7 days of enrollment:** The proportion of participants who require an unscheduled health care provider visit within 7 days of enrollment will be compared using Mantel-Haenszel test stratified by site and weight.

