## 7. Arrhythmias

Serious Adverse Events/Deaths will be reported separately in a similar fashion to the more general AE reports. In addition, narratives will be available for each event.

The analysis of safety outcomes will be undertaken as detailed below:

1. **Frequency of diarrheal episodes during the 48-hours following ED disposition:** The total number of episodes of diarrhea related to the presenting illness will be compared between groups (active and placebo) using a generalized linear model to compare differences between Poisson rates whilst adjusting for stratification.
2. **Maximal number of diarrheal episodes in 24 hours:** To test whether this outcome differs between the active and placebo treatments, we will use a Mann-Whitney U-test.
3. **Serious Adverse Events (SAEs):** The frequency of SAEs will be reported for both active and placebo groups. No formal testing will be undertaken.
4. **Palpitations:** The frequency of palpitations will be reported for both active and placebo groups. No formal testing will be undertaken.
5. **Pre-syncope /syncope:** The frequency of pre-syncope/syncope will be reported for both active and placebo groups. No formal testing will be undertaken.
6. **Chest Pain:** The frequency of chest pain will be reported for both active and placebo groups. No formal testing will be undertaken.
7. **Arrhythmias:** The frequency of arrhythmias will be reported for both active and placebo groups. No formal testing will be undertaken

---

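### The 7-day and 48-hour episode counts are compared with a Poisson-rate model that has no pre-specified handling of overdispersion

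*Combined protocol and SAP*

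**What the plan says.** Section 9.4.3 (analysis item 1) compares the total number of vomiting and diarrhea episodes between arms "using a generalized linear model to compare differences between Poisson rates whilst adjusting for stratification". The same section defines frequency as the total over the study and adds that it "will not consider differences in the vomiting duration across participants". Section 9.4.4 (safety analysis item 1) repeats the model for the 48 hours after ED disposition, in these words: "The total number of episodes of diarrhea related to the presenting illness will be compared between groups (active and placebo) using a generalized linear model".

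Section 9.4.1 places vomiting and diarrhea frequency in a Holm procedure in which "the smallest of the eight p-values will be compared to a significance level of" 0.05/8. It promises 95% confidence intervals for the primary and secondary treatment effects. It also contains a general safeguard: "All analytical models will be evaluated and adjustments will be made if any assumptions appear to be seriously violated".

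No link function, scale parameter, robust variance, negative binomial model or zero-inflation is named for either count.

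**The concern.** A Poisson model sets the variance equal to the mean. Three features of this trial make that unlikely.

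- A total over seven days adds up illnesses of very different length. The window is the same for every child, so the total is a legitimate outcome, but variation in duration between children adds variance beyond Poisson.
- Section 5.1 admits children with three or more vomits in 24 hours, while Section 9.4.7 defines a subgroup with more than ten. Baseline severity therefore varies widely.
- Section 9.4.7 also separates children with and without diarrhea in the preceding 24 hours. A mixture of children with no diarrhea and children with many stools has a variance above its mean. Adjusting for site and weight removes neither of these differences in baseline illness.

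If the excess variance is ignored, standard errors are too small, p-values too low and confidence intervals too narrow. Holm starts from the smallest p-value, so a Poisson p-value that is too small can pass first and relax the next threshold to 0.05/7. The safety count measures diarrhea, the harm that Sections 2.2 and 4.2 raise about repeated ondansetron.

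**Working it through.** **The plan's own figure.** The documents give no sample size, power or dispersion for the counts. The only sample-size calculation is for the binary primary outcome, and it reproduces. Section 9.2 aims to "detect an absolute beneficial treatment effect of 10% with 90% power" from a 30% control rate: "Using a two-sided type I error of 0.05 and the hypothesized proportions yields a required total sample size of 784 patients".

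n per arm = [1.96·√(2·0.25·0.75) + 1.2816·√(0.30·0.70 + 0.20·0.80)]² / 0.10² = (1.200 + 0.780)² / 0.01 = 392, so 784 in total. Inflation: 784/0.90 = 871 (stated 870), and 870/0.92² = 1028 (stated 1030). Nothing below changes these figures.

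**Inputs for the counts**
- Alpha: 0.05 two-sided, or 0.05/8 = 0.00625 at Holm's first step (Section 9.4.1).
- Strata: 6 sites × 2 weight groups = 12 (Section 4.1).
- Sample size: 784, or 1030 × 0.90 = 927 followed (Section 9.2).
- φ = variance/mean: **not in the documents**, so a range is shown.

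**Effect of ignoring φ.** The Poisson standard error is too small by a factor √φ, so

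type I error = 2·[1 − Φ(z_crit/√φ)] and CI width relative to correct = 1/√φ.

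With z_crit = 1.960 (0.05) or 2.734 (0.00625):

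| φ (assumed) | Type I error at 0.05 | Type I error at 0.00625 | CI width vs correct |
|---|---|---|---|
| 1 | 0.050 | 0.006 | 100% |
| 1.5 | 0.110 | 0.026 | 82% |
| 2 | 0.166 | 0.053 | 71% |
| 3 | 0.258 | 0.114 | 58% |
| 5 | 0.381 | 0.221 | 45% |

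**Simulation check.** Null true, 12 strata in the model, 1500 runs per row, Monte Carlo SE about √(0.05·0.95/1500) = 0.006. Overdispersed counts are negative binomial.

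| N | Mean | Average estimated φ | Plain Poisson, 0.05 | Plain Poisson, 0.00625 | Quasi-Poisson, 0.05 | Robust SE, 0.05 |
|---|---|---|---|---|---|---|
| 784 | 1.7 | 1.00 | 0.046 | 0.007 | 0.051 | 0.053 |
| 927 | 1.7 | 1.00 | 0.057 | 0.006 | 0.059 | 0.060 |
| 784 | 1.7 | 2.65 | 0.255 | 0.114 | 0.062 | 0.063 |
| 927 | 1.7 | 2.67 | 0.233 | 0.095 | 0.054 | 0.053 |
| 927 | 5.0 | 3.48 | 0.313 | 0.144 | 0.056 | 0.056 |
| 784 | 1.7 | 4.85 | 0.385 | 0.233 | 0.060 | 0.059 |
| 927 | 1.7 | 4.88 | 0.384 | 0.228 | 0.065 | 0.062 |

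The simulation agrees with the formula. Both corrected methods stay near 5% throughout, and when φ is 1 they differ little from plain Poisson.

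**How a mixture raises φ (illustration).** If a share z of children have no diarrhea and the rest are Poisson, φ = 1 + mean·z/(1 − z). Take 2.3 episodes, the 48-hour placebo mean of the 145-child trial in Section 2.2. An assumed z of 0.3 gives 1 + 2.3·0.3/0.7 = 2.0, and an assumed z of 0.5 gives 1 + 2.3 = 3.3. The values of z are not from the documents.

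**The case against.** **Do the cited trials prove heavy overdispersion?** A reader might infer this from Section 2.2. In the 145-child trial 46% of the placebo arm vomited by 24 hours, so 54% did not. In the 109-child trial the placebo mean was 1.7 over 24 hours, and a Poisson mean of 1.7 implies only 18% zeros. Matching both figures gives φ of about 2.9 (zero-inflated Poisson) or 5.9 (negative binomial). The documents do not support that inference:

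- No variance or standard deviation of any count is reported.
- The zero share and the mean come from different trials. In the active arms the same pairing is impossible: 42% vomiting requires a mean of at least 0.42, but the other trial's mean was 0.2.
- In the 145-child trial "the median number of vomiting episodes remained zero, with no statistically significant difference between groups". With 46% vomiting, that fits a Poisson mean of −ln(0.54) = 0.62 with no overdispersion.
- The one diarrhea comparison with a P value, 5.0 versus 4.3 episodes (P = 0.04, N = 109), points the other way. Assuming equal arms and a Wald-type test, the Poisson SE is √(9.3/54.5) = 0.41, z = 1.69 and P = 0.09, so the implied φ is (1.69/2.05)² ≈ 0.7. The test used is not stated, so this does not establish equal mean and variance either.

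**The plan has a safeguard.** The clause in Section 9.4.1 covers every model, and φ of 3 or more would be a serious violation. A generalized linear model also does not exclude an estimated scale. An unadjusted Poisson result is therefore a risk, not something the plan prescribes. This stands. But the clause gives no diagnostic, threshold or fallback. Section 9.4.6 lets the data-center biostatisticians see results by arm, though not which arm is which. Section 9.4.2 shows how a fallback can be fixed in advance: a Mantel-Fleiss value below 5 triggers the exact test.

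**Other limits.** Sections 9.4.6 and 9.4.9 refer to a study SAP that may hold more detail. Vomiting is also tested by Van Elteren and Mantel-Haenszel methods, and maximal diarrhea by Mann-Whitney; none of these relies on Poisson variance. At Holm's first step the error rates are lower than at 0.05. All of this limits the size of the point but does not remove it.

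**Conclusion.** The point holds as a gap in pre-specification. Both count analyses name a Poisson-rate model and leave the treatment of overdispersion open until the data are seen. Overdispersion is likely on design grounds, but its size cannot be taken from the documents.

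The consequence is conditional on an assumed φ and on no correction being made. Even a ratio of 2 would more than triple the nominal 5% error, to about 17%, and at Holm's first step would raise 0.6% to about 5%. If φ is close to 1, nothing is wrong with the planned test. Statements that the cited data show heavy overdispersion, or that the intervals will certainly be far too narrow, go beyond the evidence.

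This should be fixed, with moderate confidence. The primary outcome, its test and the sample size of 784 (1030 randomized) are not affected.

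**What to change.** Before unblinding, name one method for both the 7-day counts (Section 9.4.3) and the 48-hour diarrhea count (Section 9.4.4). Either of these would do:

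- log-link Poisson regression with robust (sandwich) standard errors, or
- negative binomial regression.

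Adjust for site and weight stratum and report rate ratios with 95% confidence intervals. The choice between the two is partly preference; what matters is that it is fixed in advance and does not depend on a look at the dispersion. The clause in Section 9.4.1 can then remain as a general safeguard.

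The cost is a few words in the SAP. If the counts are overdispersed, the confidence intervals will be wider than plain Poisson would give; if they are not, almost nothing changes. No new data and no change to sample size are needed.

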## 4 STUDY DESIGN

### 4.1 OVERALL DESIGN

We will conduct a Phase III multi-centre, 2-arm, placebo-controlled, double-blind, parallel design randomized controlled trial comparing the effectiveness and adverse event profile of multiple dose (as needed) oral ondansetron compared with placebo when administered to children with acute gastroenteritis (AGE)-associated

vomiting following ED discharge. The study will be stratified by site (6 sites) and weight (< 20kgs and ≥ 20kgs). Weight is being employed, rather than age, as dosing is weight based.

We hypothesize that the administration of ondansetron post-ED discharge will be associated with improved outcomes as compared with placebo.

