## 6.3 MEASURES TO MINIMIZE BIAS: RANDOMIZATION AND BLINDING

**Sequence Generation:** A biostatistician will generate a randomization list stratified by site and weight, which will then be uploaded to an internet based randomization service that uses random-number generating software. The lists will be sent to the central research pharmacy located in Calgary, Alberta who will disseminate the lists to the appropriate site research pharmacies. Kits will be prepared and labelled on site at each participating institutional research pharmacy. The kits will be stored in the local site research pharmacies until dispensed to the ED for recruitment needs.

**Allocation Concealment:** Randomize.net uses industry standard security to send data over the internet. Randomization will be blocked using random blocks of 4 and 6 with a 1:1 allocation ratio. Stratifying by clinical site and weight and blocked randomization will ensure that variations (e.g. site specific practice patterns, gastrointestinal pathogens) are comparably distributed across treatment arms. Only the research pharmacy at the coordinating centre and www.randomize.net will retain the randomization code.

**Implementation:** Potentially eligible patients will be screened. A log of all screened patients will be maintained. If eligible, the details of the study will be discussed with the caregivers and potential patients. If consent is obtained, enrolled participants will be assigned a participant ID number by the clinical site via REDCap (i.e record ID). Baseline demographic clinical variables will be collected and the data collection forms will be completed either on paper or directly into the secure online REDCap database via electronic tablet. The research team member will

then log into randomize.net which will randomize the patient (i.e. it will provide a kit number that corresponds to a study drug kit at the clinical site which will be given to the patient).

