5. **Proportion of participants who receive intravenous rehydration:** The proportion of participants who receive intravenous rehydration will be compared using Mantel-Haenszel test stratified by site and weight. If the number of participants requiring intravenous rehydration is low then exact calculations without stratification may be required.
6. **Caregiver satisfaction as measured by a 5-point Likert scale in the 48 hours following ED disposition:** Caregiver satisfaction with the therapy provided (oral ondansetron or placebo) in the 48 hours following ED disposition will be compared using a Mann-Whitney U Test.

---

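### Caregiver satisfaction and maximal diarrhea are tested without the randomisation strata, and IV rehydration may be; aligning them with the rest of the plan is a free improvement

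*Combined protocol and SAP*

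**What the plan says.** Section 4.1 sets the strata: "The study will be stratified by site (6 sites) and weight", with two weight bands, which makes 6 × 2 = 12 strata. Section 6.3 adds the mechanism, "Randomization will be blocked using random blocks of 4 and 6 with a 1:1 allocation ratio", and the purpose: balancing differences such as local practice and pathogens across the arms.

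Most analyses follow the design. In section 9.4.2 the primary Mantel-Haenszel test controls for the strata. In section 9.4.3 the planned tests for any vomiting, unscheduled visits and IV rehydration are Mantel-Haenszel by site and weight. The Poisson models for vomiting frequency (9.4.3) and 48-hour diarrhea frequency (9.4.4) adjust for stratification.

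Four items differ, and no reason is given:

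- Caregiver satisfaction (9.4.3, analysis item 6) "will be compared using a Mann-Whitney U Test".
- Maximal diarrheal episodes in 24 hours (9.4.4, analysis item 2): "we will use a Mann-Whitney U-test".
- IV rehydration (9.4.3, analysis item 5): if counts are low, "then exact calculations without stratification may be required". No threshold for low is given.
- Vomiting duration (9.4.3, analysis item 2) "will be compared using the Van Elteren test, stratified by center and duration of symptoms (pre-enrollment". The symptom-duration categories are not defined there. A split at 48 hours appears only among the baseline characteristics (9.4.1) and the exploratory covariates (9.4.2).

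**The concern.** Blocked randomisation within strata removes between-stratum differences from the treatment comparison. A test that ignores the strata still counts those differences as noise. Its standard error is then too large whenever site or weight predicts the outcome, and the test rejects less often than its nominal level.

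Satisfaction belongs to the Holm family of section 9.4.1, whose first step is 0.05/8, so lost power is not trivial there. For maximal diarrhea, a conservative test makes harm slightly harder to see. Section 2.2 cites two earlier trials with more diarrhea on ondansetron, and section 4.2 names this as the risk to weigh against benefit.

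For IV rehydration the issue is also one of pre-specification. The plan holds two low-count rules for the same kind of test. The primary outcome has a defined trigger and keeps its strata. IV rehydration has an undefined trigger and drops them, which leaves a choice to be made after the counts are seen.

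**Working it through.** **The plan's own figure.** The plan gives no power or precision for any secondary or safety test. Its one sample size (9.2; 30% vs 20%, 90% power, two-sided 0.05) reproduces:

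n per arm = [1.960·√(2·0.25·0.75) + 1.282·√(0.30·0.70 + 0.20·0.80)]² / 0.10² = 391.9, so 392 per arm and 784 in total.

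That figure concerns the primary outcome, whose test uses the strata, so nothing below changes it.

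**Cost of ignoring the strata.** Let R² be the share of outcome (rank) variance explained by site and weight. The documents give no value, so 0 to 0.15 is an assumed range. Let θ be the noncentrality of the stratified test; for 80% power at two-sided 0.05, θ = 1.960 + 0.842 = 2.802. With balance within strata, the unstratified test has:

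- size = 2·[1 − Φ(1.960/√(1−R²))]
- power = 1 − Φ(1.960/√(1−R²) − θ)

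Example, R² = 0.10: 1.960/√0.90 = 2.066; size = 0.039; power = Φ(2.802 − 2.066) = Φ(0.736) = 0.769.

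| R² (assumed) | Size | Power (stratified test: 0.800) |
|---|---|---|
| 0 | 0.050 | 0.800 |
| 0.01 | 0.049 | 0.797 |
| 0.02 | 0.048 | 0.794 |
| 0.05 | 0.044 | 0.785 |
| 0.10 | 0.039 | 0.769 |
| 0.15 | 0.034 | 0.750 |

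At the first Holm step (0.05/8 = 0.00625; θ = 2.734 + 0.842 = 3.576), 80% becomes about 0.78, 0.76 and 0.73 for R² of 0.05, 0.10 and 0.15.

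The formula assumes that the balance created by randomisation is intact. Maximal diarrhea is a safety outcome, and section 9.3 limits the safety population to children who took a dose, so balance there is only approximate. If it were lost entirely, size would return to 0.05 and power at R² = 0.10 would be Φ(2.802·√0.90 − 1.960) = Φ(0.698) = 0.757. The picture hardly moves.

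**Simulation check, five-category satisfaction score.** Assumptions: 928 children (about 1030 × 0.90), 12 strata, blocks of 4 and 6, unequal site sizes, 1,500 runs per case, Monte Carlo standard error about 0.01. Power of Mann-Whitney against Van Elteren by site and weight:

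- no stratum effects: 0.821 vs 0.821
- site 2%, weight 1% of variance: 0.843 vs 0.848
- site 5%, weight 5%: 0.840 vs 0.857

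The losses run from nil to about 2 points, in line with the formula.

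**Vomiting duration.** Same set-up, with about half the children having no vomiting. Columns give the stratification used.

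| Variance from site / weight / symptom duration | Site × duration (plan) | Site × weight | All three |
|---|---|---|---|
| 0 / 0 / 0 | 0.784 | 0.789 | 0.783 |
| 2% / 1% / 5% | 0.812 | 0.796 | 0.810 |
| 2% / 1% / 10% | 0.829 | 0.794 | 0.823 |
| 5% / 5% / 5% | 0.809 | 0.810 | 0.811 |
| 5% / 5% / 0 | 0.799 | 0.815 | 0.800 |
| 2% / 10% / 1% | 0.802 | 0.833 | 0.834 |

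Against site × weight, the planned test ranges from 3.5 points better (0.829 − 0.794) to 3.1 points worse (0.833 − 0.802). All three factors together stay within 1.5 points of the better two-factor choice.

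**IV rehydration.** Here the comparison is textual. Section 9.4.2 has a Mantel-Fleiss check and, for a value below 5, an exact Mantel-Haenszel test that keeps the strata. Section 9.4.3 has low counts, undefined, and an exact calculation that drops them. The first rule can be applied to IV rehydration unchanged.

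**The case against.** The strongest reply is that the loss is conditional and small. Nothing is lost if site and weight do not predict the outcome, and the documents contain no R² for these endpoints. The only nearby evidence, in section 3, is a non-significant difference in MVS between institutions (P = 0.11; 11 centres, 455 children). If that came from a one-way analysis of variance (assumption), F(10, 444) is about 1.58 and R² = 15.8/(15.8 + 444) = 3.4%, which puts power near 0.79. This is for the total score rather than for satisfaction or diarrhea, and it leaves weight out, but it does not suggest a large effect. This objection stands as to size. It does not explain why these tests differ from the others.

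It is also fair that IV rehydration is planned as a stratified test, that the fallback is conditional, and that the section 9.4.2 rule was written for the primary outcome. Both exact methods are valid. What remains is the undefined trigger and the needless loss of strata.

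A reader might infer more than the documents support:

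- *That replacing weight by symptom duration weakens the vomiting-duration test.* Not shown. Centre is kept, and symptom duration may predict vomiting duration better than weight does. Section 9.4.2 lists it as a covariate for the primary outcome and does not list weight; section 4.1 ties the choice of weight to dosing.
- *That the unstratified tests are invalid.* They err on the conservative side.
- *That secondary power is already short.* No secondary power figure is given.
- *That safety testing in general ignores the strata.* Of the two formally tested safety outcomes, one adjusts for them.

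**Conclusion.** The point holds as a free improvement. Two tests, satisfaction and maximal diarrhea, omit the strata without a stated reason, and the IV rehydration fallback would omit them although the plan already contains a stratified alternative. If site and weight explain 0 to 10% of outcome variance (assumed), a stratified test with 80% power drops to about 77–80% at two-sided 0.05 when the strata are ignored. Type I error is not inflated. The primary analysis and the sample size are untouched.

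For vomiting duration no loss is established. The only firm gap there is that the symptom-duration categories are not stated where the test is defined.

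**What to change.** Amend sections 9.4.3 and 9.4.4:

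1. Caregiver satisfaction and maximal diarrheal episodes in 24 hours: replace the Mann-Whitney test by a Van Elteren test stratified by site and weight.
2. IV rehydration: replace the undefined low-count clause by the section 9.4.2 rule, that is, the Mantel-Fleiss criterion and, if it is below 5, the exact Mantel-Haenszel test by site and weight.
3. Vomiting duration: keep centre and symptom duration, and write the categories (under 48 hours; 48 hours or more) into the item. Optionally add weight as a third factor; it should not displace symptom duration.

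If any departure from the strata is intended, one sentence giving the reason would do instead. The cost is wording only. Site and weight are already recorded for randomisation, so no new data or participants are needed. The change should be made before any results by arm are seen.
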